### 2.11. Statistical Analysis

All statistical analyses will be conducted using IBM SPSS Statistics, version 30.0.0, and R, version 4.5.0. The threshold for statistical significance will be set at α = 0.05. Two-tailed tests will be used unless a specific directional hypothesis is stated (e.g., the anticipated superiority of ETV over VPS), in which case one-tailed tests will be applied.

Continuous variables will first be tested for normality using the Kolmogorov–Smirnov test, and for homogeneity of variance using Levene’s test. If assumptions of normality and homoscedasticity are met, parametric tests such as the independent-samples *t*-test will be used. For repeated measures data, linear mixed-effects models will be applied instead of a traditional ANOVA to account for intra-subject variability and missing data points. If assumptions are violated, appropriate non-parametric alternatives (e.g., Mann–Whitney U test, Wilcoxon signed-rank test) will be applied.

To control Type I errors in multiple comparisons, a Bonferroni correction will be applied where appropriate. In addition to *p*-values, effect sizes (e.g., Cohen’s d for *t*-tests, η^2^ or partial η^2^ for ANOVA) will be reported to quantify the magnitude of observed effects.

For the analysis of longitudinal data, mixed-effects models will be used to account for intra-subject variability across follow-up points. These models will include fixed effects for time and the treatment group, as well as random intercepts to capture individual-level variability.

An a priori power analysis was performed assuming an effect size of Cohen’s d = 0.5, power (1 − β) of 0.80, and α = 0.05 (two-tailed). The estimated required sample size was 51 participants per group. This effect size was selected as a conservative estimate based on previously published studies evaluating pre- and postoperative cognitive and motor changes in patients with iNPH. Nonetheless, we recognize that this estimate may be optimistic. If the true effect is smaller, a larger sample size would be needed to retain adequate statistical power. This limitation is acknowledged, and future extensions of the study may involve adaptive or sequential design strategies to account for observed variability.

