The primary outcome will be the change in cognitive and motor performance over time. Cognitive functions will be evaluated using neuropsychological tests, focusing on memory, attention, executive function, and language. All cognitive assessments will be conducted both preoperatively and at each postoperative follow-up interval, as stated in the protocol. Motor outcomes will be assessed through gait analysis and coordination tests. All motor assessments will likewise be performed preoperatively and postoperatively using standardized tools including the Timed Up and Go (TUG) Test, the Baiobit wearable system, and the iNPH grading scale. The preliminary expectations are that patients in both the ETV and VPS groups will experience significant improvements in gait, as gait disturbance is typically the first symptom to improve following iNPH surgery. However, the degree of cognitive improvement may differ between the two groups, as prior evidence suggests that early intervention and reduced white matter compression may promote better cognitive recovery. By comparing cognitive trajectories in the ETV and VPS groups, this study aims to determine whether ETV has comparable or superior cognitive benefits relative to VPS. Structural changes in the brain will be analyzed using diffusion tensor imaging (DTI) and magnetic resonance imaging (MRI) with flowmetry. DTI will track changes in white matter integrity over the 12-month follow-up period. Since periventricular white matter is particularly vulnerable in iNPH, changes in the integrity of white matter tracts, such as the corticospinal tract, will be examined. The integrity of these tracts is essential for motor coordination and cognitive functions. Tractography will be used to visualize white matter pathways before and after surgery, providing insight into how ETV and VPS differentially affect white matter recovery. Neurophysiological changes will be measured using navigated transcranial magnetic stimulation (nTMS). This technique will allow researchers to assess motor cortical excitability and map changes in corticospinal tract connectivity. Motor evoked potentials (MEPs) will be recorded before surgery and at all follow-up intervals. An increase in MEP amplitude after surgery would suggest improved cortical excitability and the potential recovery of motor function. Differences in MEP amplitudes between the ETV and VPS groups may offer additional evidence regarding which procedure promotes superior motor recovery. Secondary outcomes will include the rate of complications, intensive care unit (ICU) stay, and patient-reported quality of life. Patients in the VPS group are expected to have a higher incidence of device-related complications, such as infection, shunt malfunction, and over-drainage, compared to the ETV group, which does not require the implantation of a foreign device. ICU stay and hospital length of stay will be compared between the two groups, with the hypothesis that ETV patients will have shorter stays due to the less invasive nature of the procedure. Quality-of-life measures will be obtained from patient self-reports, providing insight into the broader impact of surgery on daily living and well-being.

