
### Primary and Secondary Endpoints

This study’s primary outcome is the quantification of improvement in cognitive and motor performance from baseline to 12 months after VPS surgery or ETV. Secondary outcomes include the rate of postoperative complications (e.g., infection, device malfunction, or over-drainage), length of hospitalization, ICU stay, and patient-reported quality of life. To ensure that the study has sufficient power to detect meaningful differences between the two surgical groups, a power analysis was conducted. This analysis determined that a total sample size of 100 patients (50 in each group) would be required to achieve a power of 80% to detect an effect size (d) of 0.5 at a significance level of 0.05. The randomized controlled trial design, combined with standardized surgical protocols and the use of advanced neuroimaging and neurostimulation techniques, ensures that the results will be both statistically robust and clinically relevant.

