### 4.1. VPS Versus ETV: Pros and Cons

The surgical treatment of iNPH is centered around two main approaches: endoscopic third ventriculostomy (ETV) and ventriculoperitoneal shunt (VPS) [9]. Each of these procedures offers distinct benefits and limitations, making the choice of treatment highly dependent on patient-specific factors, anatomical characteristics, and clinical goals. One of the key advantages of ETV is the elimination of the need for an implantable device [41]. Unlike VPS, which relies on a catheter and valve system to drain cerebrospinal fluid (CSF) from the brain to the peritoneal cavity, ETV creates a natural internal pathway for CSF flow. This approach avoids the risk of mechanical failure, disconnection, and infection associated with implanted devices. By removing the dependency on an external device, ETV reduces the overall burden on healthcare systems, as it does not require lifelong device monitoring or replacement surgeries. Another important advantage of ETV is the reduced risk of postoperative infection. Since no foreign object is implanted, the likelihood of infection is significantly lower compared to VPS, where the presence of an implanted shunt system increases susceptibility to bacterial colonization. ETV also provides a long-term solution for many patients, as it re-establishes the body’s natural CSF flow dynamics, thereby reducing the need for future surgical revisions [42,43]. Unlike VPS, where shunt failure often necessitates additional surgeries, ETV patients are less likely to require repeat procedures. Additionally, the absence of complications related to over-drainage, which is a known risk of VPS, further highlights the stability and sustainability of ETV. Over-drainage, often seen in VPS patients, can result in subdural hematomas, but this risk is inherently avoided in ETV due to its reliance on natural flow mechanisms. Moreover, ETV has been associated with shorter hospital stays, fewer intensive care unit (ICU) admissions, and faster recovery times. Given the minimally invasive nature of the procedure, patients often experience less postoperative discomfort and a quicker return to daily activities compared to those who undergo VPS. Despite these advantages, ETV also has certain limitations that must be considered when selecting a treatment for iNPH. A critical disadvantage of ETV is its dependence on patient-specific anatomical factors [9]. The procedure requires sufficient anatomical space within the third ventricle and basal cisterns to safely create a new pathway for CSF flow. In patients with anatomical anomalies, such as a narrow or distorted third ventricle floor, ETV may be technically infeasible. Furthermore, ETV is a more technically demanding procedure that requires specialized neurosurgical skills and advanced neuronavigation technology. The surgeon must ensure that the perforation of the third ventricle floor does not damage critical adjacent structures, such as the basilar artery, as such damage could lead to severe complications, including stroke. Another significant challenge with ETV is the risk of stoma closure. Over time, the opening created in the third ventricle may close due to scarring or the accumulation of cellular debris, thereby blocking the CSF flow and necessitating additional surgical intervention. Unlike VPS, which allows for shunt adjustments, ETV does not offer a means for mechanical control or adjustment after the surgery is complete. Additionally, while ETV is generally effective for resolving gait disturbances, the evidence regarding its impact on cognitive recovery is mixed. Cognitive improvements after ETV are often slower and less predictable, as cognitive recovery depends on the restoration of periventricular white matter pathways. Delayed cognitive recovery may be attributed to the slow process of white matter reorganization following the release of ventricular compression. From a patient-centered perspective, ETV would provide a better quality of life, as it would eliminate the need for a permanent shunt and reduce the risk of repeated surgical interventions. This outcome would also have economic benefits, as VPS requires frequent monitoring, shunt revisions, and hospitalization for complications, whereas ETV offers a more definitive, one-time solution.

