
On the other hand, VPS offers a different set of benefits that make it a widely used approach for the treatment of iNPH. One of its most notable advantages is its applicability to a broader range of patients [9,41,42,43,44]. Unlike ETV, which requires a specific anatomical configuration to be effective, VPS can be used in almost all patients with iNPH, regardless of their ventricular anatomy. This versatility allows neurosurgeons to treat patients who would otherwise be ineligible for ETV due to unfavorable anatomical features, such as narrow ventricles or the presence of subarachnoid scarring. VPS also provides a more predictable and immediate resolution of symptoms. Many patients experience an almost immediate improvement in gait, balance, and motor coordination following the procedure [9,41,42,43,44,45]. This immediate symptom relief can have a profound impact on patient quality of life, especially in those with severe gait impairments. The procedure is well-documented, and its effectiveness has been established through decades of clinical practice and research. Neurosurgeons are highly familiar with VPS procedures, and well-established surgical protocols ensure a high degree of predictability in outcomes. This predictability extends to the management of complications as well. Since VPS systems are widely used, shunt components, valves, and catheters are readily available, and the replacement of faulty or malfunctioning components is straightforward. The design of modern shunt systems, which often includes programmable valves, allows neurosurgeons to adjust the flow rate of CSF drainage as needed, offering greater control over the treatment process. Nevertheless, VPS is not without its drawbacks. One of the most significant disadvantages of VPS is the patient’s lifelong dependence on an implanted device. Once the shunt is placed, the patient becomes reliant on its continued functionality to maintain normal CSF dynamics. If the shunt fails—due to a blockage, disconnection, or mechanical malfunction—the patient may experience a rapid return of iNPH symptoms, such as gait instability and cognitive decline, necessitating immediate medical attention. The risk of shunt failure is substantial, with studies reporting that up to 40% of VPS patients require at least one shunt revision during their lifetime [9,41,42,43,44,45,46]. Revision surgeries are costly, invasive, and increase the patient’s risk of infection, anesthesia-related complications, and further surgical trauma. Infection is another critical concern with VPS, as the introduction of a foreign device into the body creates an opportunity for bacterial colonization. Shunt infections can be difficult to treat, often requiring removal of the device, intravenous antibiotic therapy, and subsequent re-implantation. In some cases, infection-related complications result in prolonged hospital stays and increased healthcare costs. VPS also carries a risk of over-drainage, which occurs when too much CSF is drained from the brain’s ventricles, resulting in subdural hematomas. This complication is particularly concerning for elderly patients, whose brains are more susceptible to the effects of over-drainage due to brain atrophy. Over-drainage can result in significant neurological deficits and may necessitate emergency intervention. Additionally, VPS patients require long-term follow-up to monitor shunt function and detect potential malfunctions. Unlike ETV, which is often a “one-and-done” procedure, VPS requires continuous oversight and lifetime device monitoring [9,41,42,43,44,45,46]. These follow-ups place a financial and logistical burden on both patients and healthcare systems, as they involve regular check-ups, radiological evaluations, and emergency revisions when problems arise.

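### The one longitudinal model stated has no group-by-time term, so as written it cannot compare trajectories or estimate the ETV minus VPS difference in change from baseline to 12 months

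*Protocol article*

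**What the plan says.** Section 2.11 (Statistical Analysis) sends repeated measures to mixed models: "For repeated measures data, linear mixed-effects models will be applied instead of a traditional ANOVA to account for intra-subject variability and missing data points". It later says that "mixed-effects models will be used to account for intra-subject variability across follow-up points", and gives the terms: "These models will include fixed effects for time and the treatment group, as well as random intercepts to capture individual-level variability". The article names no group-by-time interaction, baseline covariate or change-score response. The same section lists the independent-samples t-test for continuous variables in general, without tying it to an outcome or visit.

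The question to be answered is put in two ways. Under Primary and Secondary Endpoints the "primary outcome is the quantification of improvement in cognitive and motor performance from baseline to 12 months". Section 3 (Expected Results) has "The primary outcome will be the change in cognitive and motor performance over time", and states the comparative aim with the words "By comparing cognitive trajectories in the ETV and VPS groups". Section 3 also counts the preoperative baseline among the analysed occasions, along with 1 week, 3, 6 and 12 months.

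**The concern.** A model with additive effects of time and group describes two parallel lines. If it is fitted to scores that include baseline, the modelled difference between arms in change from baseline to any visit is zero by construction. What it reports as the treatment effect is the average level difference over all visits, including the visit before surgery. If it is fitted to change scores at the follow-up visits, the group term is the average difference in change over those visits. Neither is the difference at 12 months, and neither shows whether the trajectories differ.

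An analyst who follows the sentence would therefore report a treatment effect for a quantity other than the stated primary outcome. Visits as early as 1 week after surgery would carry the same weight as the 12-month visit.

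**Working it through.** **Plan's own figure.** The plan gives no figure for this model. Its only calculation is a two-group one with d = 0.5, 80% power and α = 0.05: 51 per group, labelled two-tailed, in section 2.11, and 50 per group under Primary and Secondary Endpoints. Two-tailed, that calculation needs 63 (normal) or 64 (t-test) per group; one-tailed it needs 50 or 51. This mismatch is a separate matter, and nothing below depends on it.

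**Inputs from the article.** 50 per arm; visits at baseline, 1 week, 3, 6 and 12 months; α = 0.05; 0.5 taken from the power statement as the true 12-month difference.

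**Assumptions, because the article gives no values.** SD of 1 at each visit (0.5 is read in that unit); equal within-patient correlation ρ of 0.3, 0.5 or 0.7; complete data; two-sided test; normal approximation. Arm differences at the five visits:
- constant effect: 0, 0.5, 0.5, 0.5, 0.5
- building effect: 0, 0, 0.2, 0.35, 0.5
- crossing effect, for illustration only: 0, −0.5, −0.25, 0.25, 0.5

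**Step 1: what the group coefficient estimates.** With balanced data it is the plain mean of the visit differences.

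| Profile | Scores at 5 visits, baseline included | Change at 4 follow-up visits | 12-month change contrast |
|---|---|---|---|
| Constant | (0 + 4 × 0.5)/5 = 0.40 | 2.0/4 = 0.50 | 0.50 |
| Building | 1.05/5 = 0.21 | 1.05/4 = 0.26 | 0.50 |
| Crossing | 0/5 = 0 | 0/4 = 0 | 0.50 |

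**Step 2: standard errors.** With 2/n = 2/50 = 0.04:
- Group coefficient, five visits: √{0.04 × [ρ + (1 − ρ)/5]} = 0.133, 0.155, 0.174 at ρ = 0.3, 0.5, 0.7.
- Group coefficient, change at four visits: √{0.04 × 1.25 × (1 − ρ)} = 0.187, 0.158, 0.122.
- 12-month minus baseline contrast: √{0.04 × 2 × (1 − ρ)} = 0.237, 0.200, 0.155.

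**Step 3: power, Φ(effect/SE − 1.96), plus the negligible opposite tail.**

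| ρ | 5 visits, constant (0.40) | 5 visits, building (0.21) | 4 changes, constant (0.50) | 4 changes, building (0.26) | 12-month contrast (0.50) |
|---|---|---|---|---|---|
| 0.3 | 85% | 35% | 76% | 29% | 56% |
| 0.5 | 73% | 27% | 88% | 38% | 71% |
| 0.7 | 63% | 23% | 98% | 57% | 90% |

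**Step 4: simulation check.** Mixed models were fitted to 200 simulated trials per profile at ρ = 0.5, with all five visits in the response. For the constant profile, the mean group coefficient was 0.39 (73% rejection) and the 12-month interaction estimate was 0.50 (72% rejection). For an effect growing linearly to 0.5 at 12 months, the group coefficient was 0.17 (21%; closed form 0.18) and the interaction estimate 0.50 (71%).

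**Reading.** The estimand problem appears in every profile except one: a constant effect analysed as change at follow-up visits. Power is a different matter. For a constant effect, the averaging model beats the 12-month contrast at ρ = 0.3 with baseline in the response (85% against 56%), and at all three correlations if change is the response.

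**The case against.** Five objections deserve an answer.

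1. **The mixed model is not named as the primary analysis.** This is correct. A reader might infer that the trial has no method able to test its primary question, but the article does not support that. A t-test on 12-month change would do so, and the Cohen's d calculation fits a two-group comparison. The limit is that the t-test is never assigned to that outcome, while repeated measures are directed to the mixed model.

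2. **The sentence is a short, non-exclusive description, and an unseen analysis plan may add the interaction.** It may. However, the article chose to list the fixed and random effects, and the listed set does not match the endpoint. This is therefore a stated rule, not an omitted detail.

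3. **Baseline may not be in the response.** Section 2.11 speaks of follow-up points, while section 3 counts baseline as an analysed occasion; both readings are open. If change is modelled, the shrinkage to 0.40 under a constant effect disappears. The average over four visits remains, and for a building effect it is 0.26, not 0.50.

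4. **Does the protocol itself predict non-parallel curves?** A reader might infer this from section 4.1, which says "VPS also provides a more predictable and immediate resolution of symptoms" and "Cognitive improvements after ETV are often slower and less predictable". The first remark is explained there by gait, balance and motor coordination; the second concerns cognition after ETV and is set against ETV's own effect on gait. They do not compare the arms on one outcome, and nothing in the article predicts a crossing profile. The zero in the table is only an illustration.

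5. **Random intercepts are a conventional choice.** Agreed. Asking for an unstructured covariance would be a preference, and the point does not rest on it.

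**Conclusion.** The point holds for the mixed model as written: it cannot compare trajectories and does not estimate the difference between arms in change from baseline to 12 months. That follows from the listed terms and needs no numerical assumption. The size does need assumptions. For a true 12-month difference of 0.5 SD, the group coefficient lies between 0.21 and 0.50 over the constant and building profiles and the two readings of the response, whereas the 12-month contrast is 0.50 throughout.

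The contrast's power of 56% to 90% depends on correlations of 0.3 to 0.7, which the article does not give. It would be wrong to conclude that the interaction model always has more power; where the effect is constant it can have less. The case for changing the model is that the analysis should estimate the stated outcome.

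**What to change.** In section 2.11, add a group-by-visit term with visit as a categorical factor, and say whether baseline is part of the response or a covariate. Define the primary estimate as the ETV minus VPS difference in change from baseline at 12 months, taken from that model, for each primary measure. Make section 3, which speaks of change over time, agree with Primary and Secondary Endpoints, which fixes 12 months; the other visits then become secondary. If the t-test is meant to be the primary test instead, say so and tie it to the 12-month change. A less restrictive within-patient covariance is optional.

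The cost is a sentence or two and a few degrees of freedom, with no new data. The downside is some loss of power when the effect really is constant across visits: at low correlation if baseline is in the response, and at all three correlations examined if the alternative is a model of change scores. Using baseline as a covariate recovers part of it. At an assumed correlation of 0.6, the standard error falls from √(0.04 × 0.8) = 0.179 to √[0.04 × (1 − 0.36)] = 0.160, and power for 0.5 SD rises from about 80% to about 88%.

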The methodological approach of this study is designed to overcome many of the limitations observed in previous research. By using a randomized controlled design with a sufficiently powered sample size of 100 patients (50 in the ETV group and 50 in the VPS group), this study will provide a statistically robust comparison of the two surgical techniques. The a priori power analysis assumed a medium effect size (Cohen’s d = 0.5), α = 0.05, and power of 80%. While this provides a practical sample estimate, we acknowledge that the true effect size may be smaller than anticipated, potentially requiring a larger cohort to maintain adequate statistical power. This limitation is recognized in the design and discussed transparently.

To ensure procedural consistency across participating institutions, all surgical teams will follow a shared and standardized operative protocol, developed collaboratively by the study investigators. Pre-trial workshops and training sessions will be organized to align technical approaches and perioperative care pathways. In addition, a central monitoring committee will oversee compliance with the protocol and conduct periodic audits to mitigate variability and ensure methodological integrity throughout the multicenter implementation.

In terms of radiological criteria, the diagnosis of iNPH and anatomical suitability for surgical procedures will also be based on the validated indices. In particular, the Evans index—defined as the ratio between the maximum width of the frontal horns and the inner diameter of the skull—will be used to confirm ventriculomegaly when greater than 0.3. Likewise, the callosal angle, measured in the coronal plane through the posterior commissure, provides additional diagnostic confidence, with angles below 90° typically associated with iNPH.

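### The 51 per group labelled two-tailed is the one-tailed sample size; 50 per group gives about 70% two-tailed power at d = 0.5, not the stated 80%

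*Protocol article*

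**What the plan says.** Section 2.11 (Statistical Analysis) gives the inputs of the power analysis as Cohen's d of 0.5, power of 0.80 and α of 0.05, labelled two-tailed. Its result is: "The estimated required sample size was 51 participants per group".

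The same section sets the rule for sidedness: "Two-tailed tests will be used unless a specific directional hypothesis is stated (e.g., the anticipated superiority of ETV over VPS"; in that case one-tailed tests apply. On the choice of d it says: "This effect size was selected as a conservative estimate based on previously published studies evaluating pre- and postoperative cognitive and motor changes". It then concedes that the estimate may be optimistic and that a smaller true effect would need more patients.

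The subsection Primary and Secondary Endpoints reports the power analysis with a different result. It says that 100 patients, 50 per group, are "required to achieve a power of 80% to detect an effect size (d) of 0.5 at a significance level of 0.05". The Discussion (section 4) refers to "a sufficiently powered sample size of 100 patients (50 in the ETV group and 50 in the VPS group", and repeats d = 0.5, α = 0.05 and 80% power in the next sentence.

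The Abstract, section 2 and section 3 also give 100 patients, but attach no power to that number there.

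**The concern.** The inputs and the result are both printed, so the calculation can be repeated, and it does not reproduce. A two-tailed test at 0.05 with d = 0.5 is a standard case, and 51 per group is well short of what it needs.

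The stake is how a non-significant result will be read. The trial hypothesises that ETV is comparable or superior to VPS, and the Conclusions say that ETV could become the preferred operation if it is superior or at least non-inferior. Readers told that the trial had 80% power may take a null result as support for comparability. If the test is two-tailed, the chance of missing a true difference of d = 0.5 is about 30%, not 20%.

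**Working it through.** **Inputs, all from the protocol article**

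- d = 0.5, power 0.80, α = 0.05, labelled two-tailed (section 2.11)
- independent-samples t-test for two groups (section 2.11)
- 1:1 allocation (section 2)
- stated result 51 per group (section 2.11); planned size 50 per group (Primary and Secondary Endpoints; Discussion)

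**Step 1. Reproduce the stated figure.** The normal approximation for two means is n per group = 2(z_α + z_β)² / d², with z_β = 0.842 for 80% power.

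- Two-tailed, z_α = 1.960: 2 × (2.802)² / 0.25 = 62.8, so 63 per group.
- One-tailed, z_α = 1.645: 2 × (2.487)² / 0.25 = 49.5, so 50 per group.

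The exact noncentral-t calculation gives:

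- Two-tailed: 63.77, so 64 per group.
- One-tailed: 50.15, so 51 per group.

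The printed 51 is exactly the one-tailed t-test answer.

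**Step 2. Look for another two-tailed route to 51.**

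- A paired t-test gives 34 two-tailed and 27 one-tailed.
- Allowing for Mann–Whitney efficiency of 0.955 gives 63.77 / 0.955 = 66.8, about 67 per group two-tailed, and 50.15 / 0.955 = 52.5, about 53 one-tailed.
- Inflating for dropout only raises the two-tailed figure, for example 64 / 0.90 = 71.1, so 72 per group at an assumed 10%.

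None of these gives 51 two-tailed.

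**Step 3. Power at the planned size.** With n = 50 the standardised shift is d√(n/2) = 0.5 × 5 = 2.5. By the normal approximation, two-tailed power is Φ(2.5 − 1.960) = Φ(0.540) = 0.705, and one-tailed power is Φ(2.5 − 1.645) = Φ(0.855) = 0.804. The exact t results are:

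| n per group | Two-tailed power | One-tailed power |
|---|---|---|
| 50 | 0.697 | 0.799 |
| 51 | 0.706 | 0.806 |
| 64 | 0.801 | 0.879 |

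**Step 4. Detectable difference.** For 80% power, two-tailed, with 50 per group, the normal approximation gives d = 2.802 / 5 = 0.56. The exact t value is 0.566, or 0.57 rounded.

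**Step 5. Illustrations beyond the base case.** The documents give no dropout rate and do not say how α would be split, so these rest on assumptions. Removing 10% or 15% of patients completely gives two-tailed power of 0.65 or 0.62. Splitting α over two primary domains (0.025 each) with all 50 per group gives 0.59.

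**The case against.** The strongest defence is the sidedness clause in section 2.11. It allows one-tailed tests where a directional hypothesis is stated, and its own example is superiority of ETV over VPS. One-tailed, 50 per group has 79.9% power, which is essentially the claim. A reader might infer that the plan fixes a two-tailed primary test and that 80% is therefore simply false. The document does not support that much: two-tailed is the default, but the clause leaves the primary comparison open. What the defence cannot rescue is the label. The section calls its power analysis two-tailed, and the number is one-tailed. Nor is the stated hypothesis, comparable or superior, a clear directional claim.

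A second defence is that the article already admits a limitation. It admits only that the true effect may be below 0.5, whereas the shortfall exists at 0.5.

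Third, the 70% applies to an unadjusted t-test on one endpoint. Section 2.11 assigns longitudinal data to mixed models, partly because of missing values, so 70% is not necessarily the power of the final primary analysis. The attrition figures are illustrations under complete loss of the dropouts' data. This stands as a limit on the claim. It does not explain the 51. Baseline adjustment would bring the requirement down to about that size only with a baseline-outcome correlation near 0.45 (63 × (1 − 0.45²) = 50.2), and the article states none.

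Fourth, on the effect size, a reader might infer that d = 0.5 was taken from within-patient change and so says nothing about the difference between arms. The wording is too vague for that. It does not say whether the studies supplied changes within an arm or differences in change between arms. What stands is narrower: the same paragraph calls the value conservative and then possibly optimistic.

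Finally, the gap between 51 and 50 per group is an inconsistency, but it costs under one percentage point of power and is immaterial in itself.

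**Conclusion.** The point holds. For the inputs that section 2.11 states, the two-tailed requirement is 64 per group, and the printed 51 is the one-tailed requirement. The error carries into the two places that tie 100 patients to 80% power: Primary and Secondary Endpoints, and the Discussion. At d = 0.5 with 50 per group, two-tailed power is 0.697, about 10 percentage points below the claim; the 80% is reached only one-tailed. The difference detectable two-tailed with 80% power is d = 0.57.

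These figures assume an unadjusted two-sample t-test on a single endpoint, equal groups, complete data and no Bonferroni correction. Within those assumptions the result is exact and uses only inputs printed in the article. It is a misstatement of power together with an unresolved choice of sidedness. It does not show that the trial is too small to be worth running.

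**What to change.** 1. In section 2.11, Primary and Secondary Endpoints, and the Discussion, remove the 51 per group, the statement that 100 patients are what 80% power requires, and the description of 100 patients as sufficient. Replace them with one statement: with 50 per group and two-sided α = 0.05, power is about 70% for d = 0.5 and 80% for d = 0.57, before attrition.
2. In section 2.11, state that the primary ETV versus VPS comparison is two-sided, and take that comparison out of the one-tailed clause. Otherwise the clause would still permit a primary test that contradicts the corrected power statement.
3. In section 2.11, drop the word *conservative* for d = 0.5 and present it as the assumed difference between arms.

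The 80% should not be kept by choosing, after the fact, a baseline-outcome correlation that happens to yield it.

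The cost is wording and a less favourable stated power. No extra patients are needed. For comparison, reaching 80% two-tailed at d = 0.5 would take 2 × 64 = 128 patients, 28 more than planned, before dropout.
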